### Ongoing Monitoring of Circumcision Safety During the Trials

Please note, these estimates are based on the total populations of HIV- men enrolled in the Gates and NIH trials

Surgical and postoperative complications were expected to be ~2%, and were monitored continuously during stage one and periodically in Stage 2 (at approximately 4-7 months, ~20 and ~40 months) to ensure safety. Monitoring of the rate of complications associated with circumcision is done using similar techniques described for monitoring efficacy. To facilitate the proper analysis of this continuous safety data, we propose to use the methods of Lan, Rosenberger, and Lachin in which they demonstrate how to construct a sequential boundary (Wald boundary) for a Z‑statistic used to continuously monitoring data that maintains an overall Type I error rate. The methods build upon the spending‑function methods of Lan & DeMets, and can also be used when switching from occasional (e.g. group sequential) monitoring to continuous monitoring.

We planned to conduct interim analyses if required for DSMB safety assessment at 20 and 32 months. We expected to have completed 1,500 circumcisions by 20 months and 3,000 by 32 months. Using StatXact (Cytel Software Corp), we estimated the smallest number of AEs that would give an exact 1-sided 95% lower confidence bound on the estimated rates of AEs (not adjusted for interim analyses). With 1,250 men circumcised by 20 months, if the total AE rate  2.64% (33 events), the lower 95% CI bound would significantly exceed the expected rate of 2.0% (25 events), and for moderate/serious AEs, a lower 95% CI bound of an observed rate of 0.88% (11 events) would significantly exceed the expected rate of 0.5% (7 events). Similarly, at 32 months with 2,500 surgeries completed, if the total AE rate  2.48% (62 events), the lower 95% CI would exceed the expected 2.0% rate (50 events), and for moderate/serious AEs, with an observed rate of 0.72% (20 events), the lower 95% CI would exceed the expected rate of 0.5% (13 events)

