***Allowance for data dependent stopping:***

We propose using formal interim analysis methods for monitoring the primary outcome (incidence of HIV infection) as well as the safety aspect of the study. Lan‑DeMets group sequential methods with O'Brien‑Fleming bounds 117,118 will be utilized to ensure the maintenance of an overall Type I error rate of 5%. For monitoring HIV incidence, we anticipate one interim analysis to allow DSMB to decide whether we can commence circumcisions in the control arm, and allow sufficient time for completion of control surgeries before the end of the project. Assuming an interim analysis at project month 40, we will accrue a total of 3,028 py observation per arm, which represents 77% (3028 * 2 / 3932 * 2) of the information to be accumulated during the trial. This information fraction, for example, will give sequential O'Brien‑Fleming boundaries equal to 2.303 for the interim analysis and 2.017 for the final analysis. Without using these boundaries, we estimate (via simulation with 10,000 runs) that the overall Type I error rate wouldl be inflated to approximately 7.7%. Using these boundaries, we estimate that the Type I error rate is maintained at 0.05 and that the power for a RR of 0.53 is equal to 89.5%. Furthermore, with this RR, we estimate that there is approximately a 70% chance of crossing the boundary at the interim analysis. Sequential confidence intervals 118a will be used when reporting results. The investigators will be blinded for the interim analysis. Monitoring of safety will be done similarly, except that it will occur on a continuous basis, and will use the methods of Lan *et al.*

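### Several adverse event benchmarks in section 8.1.2 do not meet the exact one-sided 95% criterion that defines them, and one pairs a rate with a count that does not match it

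*Protocol*

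**What the plan says.** Protocol section 8.1.2 first proposes a sequential (Wald) boundary for continuous safety data "that maintains an overall Type I error rate". Under section 8.2, the paragraph on data-dependent stopping adds: "Monitoring of safety will be done similarly, except that it will occur on a continuous basis".

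Section 8.1.2 then turns to possible interim looks at 20 and 32 months and names the rule behind its counts: "we estimated the smallest number of AEs that would give an exact 1-sided 95% lower confidence bound". The same sentence marks them as "not adjusted for interim analyses". The figures are:

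- 20 months ("With 1,250 men circumcised by 20 months"): 33 total AEs (2.64%) against 2.0%, and 11 moderate/serious AEs (0.88%) against 0.5%.
- 32 months, 2,500 surgeries: 62 total AEs (2.48%) against 2.0%; for moderate/serious AEs, "with an observed rate of 0.72% (20 events), the lower 95% CI would exceed the expected rate of 0.5% (13 events".

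Just before these figures, the section says that 1,500 and 3,000 circumcisions were expected by those two dates.

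**The concern.** Each benchmark is given with a defined property, so it can be checked exactly. One fails on simple division, because its rate and its count describe different numbers of events. The others sit close enough to the edge of the criterion that a single event decides whether the property holds.

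These are the only numerical AE benchmarks the protocol gives for the 20- and 32-month looks. Someone applying the last one by its rate would flag an excess at 18 events; someone applying it by its count would wait for 20. Only the second has the stated statistical meaning. For the remaining counts, the protocol would describe an excess as established at the one-sided 5% level when the exact calculation does not show it.

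**Working it through.** **Inputs**, all from section 8.1.2: n = 1,250 and 2,500; reference rates p0 = 2.0% and 0.5%; counts 33, 11, 62 and 20; exact, one-sided, 95%.

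**Rates as printed.** 33/1,250 = 2.64%, 11/1,250 = 0.88% and 62/2,500 = 2.48% agree with the text. 20/2,500 = 0.80% does not; 0.0072 × 2,500 = 18.

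**Criterion.** For X ~ Binomial(n, p0), the exact one-sided p-value is P(X ≥ x). The exact (Clopper-Pearson) lower bound is the 5% quantile of Beta(x, n − x + 1). The bound exceeds p0 exactly when P(X ≥ x) < 0.05.

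| n | p0 | count | rate | P(X ≥ x) | lower bound | meets criterion |
|---|---|---|---|---|---|---|
| 1,250 | 2.0% | 33 (printed) | 2.64% | 0.069 | 1.938% | no |
| 1,250 | 2.0% | 34 | 2.72% | 0.048 | 2.007% | yes |
| 1,250 | 0.5% | 11 (printed) | 0.88% | 0.053 | 0.494% | no |
| 1,250 | 0.5% | 12 | 0.96% | 0.026 | 0.555% | yes |
| 2,500 | 2.0% | 62 (printed) | 2.48% | 0.054 | 1.990% | no |
| 2,500 | 2.0% | 63 | 2.52% | 0.041 | 2.026% | yes |
| 2,500 | 0.5% | 18 (printed rate) | 0.72% | 0.084 | 0.466% | no |
| 2,500 | 0.5% | 19 | 0.76% | 0.051 | 0.498% | no |
| 2,500 | 0.5% | 20 (printed count) | 0.80% | 0.030 | 0.531% | yes |

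The smallest qualifying counts are therefore 34, 12, 63 and 20.

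**Can another method reproduce the printed set?** Using P(X > x) instead of P(X ≥ x) gives 33, 11, 62 and 19. Mid-p and score methods give 34, 11, 62 and 19. Two-sided limits, Poisson, Wald and the larger denominators do not return the four printed counts either. The first variant suggests an off-by-one tail for three of the counts, but it does not explain the 20.

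**The other denominators.** At 1,500 and 3,000 surgeries the same exact rule gives 40 (p = 0.045) and 13 (p = 0.042) of 1,500, and 74 (p = 0.043) and 23 (p = 0.032) of 3,000. The printed counts applied there fall well short: 33/1,500 has p = 0.31, 11/1,500 p = 0.14, 62/3,000 p = 0.41 and 20/3,000 p = 0.12.

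**Two looks together.** With limits a1 at 1,250 and a2 at 2,500, and independent X1, X2 ~ Binomial(1,250, p0), the chance of a false signal is

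P(X1 ≥ a1) + Σ over k < a1 of P(X1 = k) · P(X2 ≥ a2 − k).

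- Printed counts: 9.7% for total AEs (33, then 62) and 6.8% for moderate/serious AEs (11, then 20).
- Corrected counts: 7.1% (34, then 63) and 4.6% (12, then 20).

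**The case against.** **The lost sign.** The comparison sign before 2.64% and 2.48% is missing from the available text. If it was a strict more than, the limits are 34 and 63 and both are right. This stands as a condition on the two total AE counts. It does not help the moderate/serious figures, where no sign is missing: 11 events are said to suffice and do not, and 0.72% fails even if read as more than 0.72% (19 events, p = 0.051).

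**Repeated looks.** A reader might infer that the counts break the promised overall error control. The protocol does not support that: the sentence introducing them says they are unadjusted, and the overall control is attached to the separate sequential boundary. Nor is it true that every per-look level fails, since 20 of 2,500 has a one-sided error of 3.0%. What remains is that the text does not say how the two approaches relate.

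**Status of the counts.** A reader might also take them for the limits on which the data and safety monitoring board (DSMB) would act. The stopping rules in section 8.9 contain no AE count, section 8.1.1 asks that severity be weighed before judging an excess, and the 20- and 32-month looks were to happen only if required.

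**Practical effect.** The shortfall in the 33, 11 and 62 counts is one event each, and the passage is written largely in the past tense. Section 10.7.3 reports moderate and severe complications of 3.6% in HIV-negative men. At that rate about 45 events would be expected in 1,250 surgeries (0.036 × 1,250) and 90 in 2,500, far above any of the disputed moderate/serious counts. This limits the weight of the point but does not make the figures correct.

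**Conclusion.** The point holds as an error in stated figures. Two moderate/serious benchmarks are wrong as written whatever the missing sign was: the rate of 0.72% does not match 20 events and would not meet the criterion, and 11 of 1,250 misses it (p = 0.053). The total AE counts of 33 and 62 also miss, by one event each, if the sign means at least. Only 20 of 2,500, taken as a count, has the stated property.

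The per-look results rest on the denominators of 1,250 and 2,500 and on the exact one-sided 95% rule that the protocol names. The two-look figures further assume looks at exactly those two points and true rates equal to the references; section 8.1.2 also mentions other review times, which would change them. They show the size of leaving the counts unadjusted, which the protocol discloses. They are not evidence that a claimed overall error rate was breached.

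**What to change.** Recalculate the line in section 8.1.2. If 1,250 and 2,500 surgeries are kept, state 34 (2.72%) and 12 (0.96%) of 1,250, and 63 (2.52%) and 20 (0.80%) of 2,500, each worded as that many events or more. If the expected 1,500 and 3,000 are the intended numbers, state 40 and 13 of 1,500, and 74 and 23 of 3,000. Use one pair of denominators throughout the paragraph.

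As a minor addition, say in one sentence that these per-look counts are descriptive benchmarks alongside the sequential boundary and give their two-look false-signal chance: about 7.1% for total AEs and 4.6% for moderate/serious AEs with the corrected counts at 1,250 and 2,500. If the other denominators are kept, that chance has to be recomputed.

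The cost is one recalculated line and one sentence. No data collection, sample size or patient procedure changes.

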## Primary Endpoint: Male HIV Incidence.

As noted above, the power to detect the efficacy of circumcision on male HIV acquisition is based on the total HIV-negative population of ~ 6,000 men, comprised of ~ 1,000 HIV-negative men in the Gates trial and 5000 men enrolled in the NIH trial. We present here the estimates for this population

***Efficacy:***

The Rakai STD Control Study78 found an incidence of 1.8/100 PY among the uncircumcised men and 0.9/100 PY among the circumcised men, with a Poisson adjusted RR = 0.53.1 We base our sample size estimates on this efficacy, and use a two-sided test with  = 0.05 and 1- = 0.80.

***Assumptions:***

We assumed two years follow up, with participants enrolled between 9-26 months of the study and follow up completed by study month 50, and an annual loss to follow up of 15% (please see feasibility). We also estimated the loss of power due to possible contamination (i.e., cross-over) of 7.5-10%.

***Allowance for contamination or reduced magnitude of anticipated efficacy:***

We previously observed a RR = 0.53 for HIV incidence in circumcised relative to uncircumcised men, and powered the study to be able to detect a lower efficacy of RR = 0.57. We also assessed potential effects of contamination as follows: Let RR* be the observed rate ratio in the presence of cross-over (p), and let RR be the true rate ratio in the absence of contamination. Then RR* = (p + [1-p] x RR)/(p x RR + [1-p]) = RR/([p x RR] + [1-p]) ([name] , pc). With p = 0.075 (i.e., 7.5% contamination), the observed RR* = 0.55. The sample size needs to be increased to account for this cross-over effect. With 2,500 men enrolled per arm we would accumulate 2,125 py in the 1st follow up year and 1,806 py in the 2nd follow up year, with a total over two years follow up = 3,932 py, which could detect a RR* ~ 0.57 with 80% power if the true RR = 0.53. (Please note this is 18.4% larger than the 3,209 py needed in the absence of contamination). Therefore, we enrolled ~ 2,500 men per arm into the NIH trial providing 3,932 py per arm.

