***Age criteria and selection of high risk groups:***

Rakai has is a mature generalized epidemic setting with relatively high incidence throughout the population. Table 5 shows male age-specific HIV incidence. Incidence is lowest among adolescents, high and sustained among men aged 20-29, and declines modestly at older ages. Exclusion of adolescent men 15-19, would exclude a group with considerable HIV incidence and which is of great importance in future programs. Restricting enrollment to the highest risk age group (20-29 years) would marginally increase incidence relative to the total male population 15-49, but would only include 39.5% of all men. Enrollment restricted to men aged 20-29 would require adding many more communities in order to maintain power, but this complicates logistics and inflates costs. Moreover, acceptability was highest (65% in ages 20-29), so self-selective acceptability would automatically over sample these highest risk age groups. We therefore proposed to enroll all consenting men aged 15-49.

***Additional Power provided by the ~ 1,000 HIV-negative men who decline VCT, enrolled in the Gates sponsored trial and approximately 500 additional HIV-negative men enrolled into the Gates trial after NIH trial enrolment is completed.***

Prior analyses have shown that persons who refuse VCT have higher risk behaviors than persons who accept VCT, and that this difference in risk profile is reflected in higher HIV incidence among the former populations. (HIV incidence was 1.5/100 py in men declining VCT versus 1.3/100 py in men accepting VCT.

We estimated that about 400 HIV-negative men would decline VCT per arm, assuming the loss to follow up and cross over rates above, we anticipated that these men would add an additional ~ 1256 py per arm, to the person time contributed by the HIV- men enrolled in the NIH trial. Thus, the total person years observation contributed by the combined populations of HIV-negative men from the two trials is 5188 py (1256 + 3,932 py per arm). This would enhance the study power to detect a lesser efficacy of circumcision, and help guard against loss of power if the assumptions regarding follow up and cross-over prove to be too conservative.

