## Analysis Plan

### Primary Endpoint, HIV incidence in Males.

This analysis will be done separately for HIV-negative men enrolled in the Gates and NIH trials, and for the combined population of HIV-negative males enrolled in both trials.

HIV incidence per 100 person-years (PY) will be estimated, assuming seroconversion occurred at the mid-point of each follow up interval. In both arms, time from enrollment will be accumulated up to 24 months of follow up. Person time will discount the postoperative period of sexual abstinence for intervention arm subjects. Baseline samples of subjects who seroconvert during the first follow up interval will be tested by detuned EIA and PCR to detect prevalent infections during the window period, and any suspected prevalent cases will be excluded from incidence analyses.

Exploratory data analysis will examine the populations in the two arms at enrollment to assess baseline comparability. HIV incidence will be determined by strata of covariates such as age, marital status, behaviors (e.g., number of partners, condom use), health status and other variables to identify potential confounders. We will also assess contamination (i.e., cross-over) among men allocated to circumcision who do not receive surgery, and among control subjects who opt to have circumcisions performed from non-Project services.

An intent-to-treat approach will be taken, and all men who enroll will be included, irrespective of whether intervention arm participants ultimately receive circumcision, or whether control arm participants crossover and receive circumcision prior to 24 months follow up. The rationale is that a proportion of enrolled men who initially accept circumcision may change their mind prior to receipt of surgery, and such men are likely to be self-selected. Because circumcision is delayed in the control arm, such self-selection could be differential between randomization groups. Therefore, in the circumcision arm, enrolled men who subsequently refuse circumcision, will be ascribed half the person time from enrollment to scheduled date of circumcision.

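### The cross-over formula for male HIV incidence equates two unequal expressions, and the stated RR* of 0.55 omits cross-over in the circumcision arm

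*Protocol*

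**What the plan says.** Protocol section 8.2 takes a true rate ratio from earlier Rakai data ("We previously observed a RR = 0.53 for HIV incidence in circumcised relative to uncircumcised men") and a control rate from the STD control study, which "found an incidence of 1.8/100 PY among the uncircumcised men". Under its assumptions it plans for "possible contamination (i.e., cross-over) of 7.5-10" per cent.

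The paragraph on contamination then defines the diluted rate ratio RR* through a chain of two expressions (outermost brackets cut off): "p + [1-p] x RR)/(p x RR + [1-p]) = RR/([p x RR] + [1-p". It continues: "With p = 0.075 (i.e., 7.5% contamination), the observed RR* = 0.55". It concludes that 2,500 men per arm give 3,932 py, enough to detect an RR* of about 0.57 with 80% power when the true RR is 0.53. On the size of the increase it says that "this is 18.4% larger than the 3,209 py needed in the absence of contamination".

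Section 8.8.1 says whose cross-over counts. Contamination is to be assessed "among men allocated to circumcision who do not receive surgery, and among control subjects who opt to have circumcisions performed from non-Project services", and all enrolled men are kept by intent-to-treat. The surgery section (6.1a) likewise labels a man randomised to circumcision who has decided against it at six months a cross-over, and follows him for two years.

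**The concern.** The first expression lets a share p of each arm take on the other arm's risk. The second drops p from the numerator, so it describes control men who become circumcised but no intervention men who stay uncircumcised. These are different assumptions, and an equals sign cannot join them.

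The choice matters because 0.55 falls inside the 0.57 that the person-years are said to detect. A reader therefore concludes that 7.5% cross-over is covered with room to spare. If the two-way value falls outside 0.57, that reassurance is lost for the 3,932 py.

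**Working it through.** **Inputs** (Protocol 8.2 unless noted): RR = 0.53; control rate 0.018 per py; p = 0.075 and 0.10; 3,932 py per arm for the NIH trial; 5,188 py per arm combined (3,932 + 1,256); two-sided alpha 0.05.

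**1. Reproducing the protocol's figures**
- Person-years: 2,500 × (0.85 + 0.85²) = 3,931, against 3,932 stated.
- A continuity-corrected two-proportion formula, with person-years as n, gives 3,210 at RR 0.53 (3,209 stated) and 3,904 at RR 0.57 (3,932 stated).
- RR* by the control-only form: 0.53 / (0.075 × 0.53 + 0.925) = 0.53 / 0.96475 = 0.549, the printed 0.55.

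**2. The two-way form**
- p = 0.075: (0.075 + 0.925 × 0.53) / 0.96475 = 0.56525 / 0.96475 = **0.586**.
- p = 0.10: (0.10 + 0.90 × 0.53) / (0.053 + 0.90) = 0.577 / 0.953 = **0.605**. The control-only form gives 0.53 / 0.953 = 0.556.
- The numerators differ by p + (1 − p)RR − RR = p(1 − RR), which is zero only if p = 0 or RR = 1.

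The largest RR detectable with 80% power at 3,932 py is 0.571 (continuity-corrected) to 0.581 (rate-difference z test). So 0.586 is just beyond it and 0.605 well beyond it.

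**3. Power under two-way cross-over**
Rate-difference z test: power = Φ(|r1 − r2| × √(py / (r1 + r2)) − 1.96).

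Example, p = 0.075, control rate held at 0.018: r2 = 0.018 × 0.5859 = 0.010546; 0.007454 × √(3,932 / 0.028546) = 2.766; Φ(0.806) = 79.0%. If cross-over also dilutes the control rate, r1 = 0.018 × 0.96475 = 0.017366, r2 = 0.018 × 0.56525 = 0.010175, and power is 77.6%.

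Each cell runs from the lowest value (continuity-corrected, control rate diluted) to the highest (z test, control rate held):

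| py per arm | p = 0.075 | p = 0.10 |
|---|---|---|
| 3,932 (NIH only) | 75.2–79.0% | 69.8–74.5% |
| 4,561 (see step 4) | 81.5–84.6% | 76.5–80.5% |
| 5,188 (combined, as stated) | 86.4–88.8% | 82.0–85.3% |

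**4. The Gates add-on**
Section 8.2 attributes 1,256 py per arm to about 400 men per arm. At the stated follow-up, 400 × (0.85 + 0.7225) = 629 py, about half. With 629 py the combined total is 3,932 + 629 = 4,561.

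**5. The percentage**
3,932 / 3,209 = 1.225, so 3,932 is 22.5% larger. The printed 18.4% is 1 − 3,209 / 3,932, a share of the larger number.

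**6. The same error in section 8.4 (female acquisition)**
With RR = 0.39 and p = 0.075, the control-only form gives 0.39 / 0.95425 = 0.409, the printed 0.41. The two-way form gives 0.43575 / 0.95425 = **0.457**. At 344 py per arm and 13.2 per 100 py, the same two methods give power of about 84–87%, so the 80% claim survives by these methods. I could not reproduce the undiluted figure there: the protocol gives 85% at RR 0.39, while the z test gives Φ(0.08052 × √(344 / 0.18348) − 1.96) = 94%. The restated power should therefore name its method.

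**The case against.** **The 0.57 target already leaves room.** This stands in part. The 80% is claimed at RR* of about 0.57, not 0.55, and that margin absorbs most of the error at 7.5%. A pooled-variance test with the control rate held gives 79.6%, within the tolerance of the method. At 10% no variant reaches 80%.

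**The protocol relies on the combined population.** This stands. Section 8.2 bases the male endpoint on about 6,000 men from both trials. A reader might infer that the endpoint is underpowered, but the stated 5,188 py do not support that. Even at 4,561 py only the 10% case becomes marginal.

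**The control-only form may match the planned analysis.** This stands in part. Section 8.8.1 credits men who refuse circumcision with only half the time from enrolment to their scheduled surgery, so they would add almost no uncircumcised time to the intervention arm. If those men contribute none, the intervention arm has 3,932 × 0.925 = 3,637 py at p = 0.075. The z statistic is (0.017366 − 0.00954) / √(0.017366/3,932 + 0.00954/3,637) = 2.95, which gives power of about 84%. At p = 0.10 it is about 82%. But that rule conflicts with the intent-to-treat statement in the same section and with two years' follow-up of cross-overs in 6.1a. It also does not make the printed equality true.

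**Other stronger readings.** A reader might infer that power is far lower because section 8.2 also quotes 1.3 per 100 py in men accepting VCT. The protocol does not give those men's circumcision status, so no control rate for uncircumcised men follows from it. Nor is the 89.5% power in the stopping paragraph mislabelled: it is stated for an RR of 0.53, the symbol that the preceding paragraph defines as the ratio without contamination.

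**Conclusion.** The equality is false, and the stated RR* of 0.55 does not fit cross-over as the protocol defines it. The two-way values are 0.59 at 7.5% and 0.61 at 10%, beyond the 0.57 used for sizing. The consequence is limited. NIH-only power falls slightly below 80% at 7.5% and clearly below it at 10%, while the combined person-years as stated keep it above 80% across the planned range.

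These figures assume the same p in both arms, cross-over from enrolment, and a control rate of 1.8 per 100 py. They do not put any result in doubt: the protocol reports that the NIH trial was stopped early for efficacy and that Gates enrolment is closed. This is a correction of stated figures, not a flaw in the design.

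**What to change.** - Delete the second expression in section 8.2, state that cross-over is assumed in both arms, and use the two-way form for the intent-to-treat analysis.
- Reconcile that form with the half-time rule for refusers in section 8.8.1 and the two-year follow-up of cross-overs in 6.1a, so that the power calculation and the analysis count the same person-time.
- Restate RR* as 0.59 (7.5%) and 0.61 (10%), with power of about 75–79% and 70–75% for 3,932 py and about 86–89% and 82–85% for 5,188 py. Check the 1,256 py; if it should be 629, give about 82–85% and 77–81% at 4,561 py.
- Change 18.4% to 22.5%.
- In section 8.4, change the RR* of 0.41 to 0.46 and restate the power with its method.

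The cost is text and figures only. No enrolment or analysis decision changes, but the stated NIH-only power becomes less favourable.
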